### Post-chemotherapy – day 1-4 post-chemotherapy

During the 4 days post-chemotherapy, participants will be asked to complete:

• One INVR questionnaire per day. The timing of completion should be at the same time of day as when they completed their previous questionnaire. This will ensure that 24 hours is assessed per questionnaire.

• One adherence questionnaire.

• The participant will consume 4 capsules per day. One before breakfast, one before lunch, one during an afternoon snack, and one before dinner. These capsules are to be consumed one hour before each meal.

### Post-chemotherapy – day 4 post-chemotherapy only

At the end of day 4, participants will be asked to complete:

• One FACT-G/FACIT-F questionnaire

• One FLIE-5DR questionnaire

• One ESAS questionnaire

• One adherence questionnaire

Supplements are consumed using the same schedule as above.

At the end of day 4, participants will no longer be required to consume the oral supplements and any unconsumed supplements, along with the questionnaire booklet, will either be collected by the research team, along with the participant questionnaire booklet, during the participant’s next visit to the hospital or sent directly to the researchers using a reply-paid envelope. Unconsumed supplements of each individual will be counted in order to determine their level of adherence to the study protocol.

### Assessment of blinding

At the end of day 4, the investigator will contact each participant to obtain information regarding the study blinding. This will be determined by asking each participant the following questions: “Do you think you received the placebo or the ginger supplement and why do you think this?”. Participants will also be asked if they have any comments or queries regarding the trial so as to gather feedback for the improvement of the study protocol for future trials.

The timing of the participant’s next chemotherapy cycle will also be discussed and arrangements will be made to meet within the week before chemotherapy in order to dispense additional supplements and assessments.

### Statistical analysis

Analyses will be conducted according to intention-to-treat principles i.e. the consent process will maximise outcome data collection and attempt to assess nausea symptoms for everyone, and will retain original group allocation despite actual compliance levels.

Participants will be block stratified by chemotherapy category (i.e. minimal, low, moderate and high emetogenicity) then randomised within strata into intervention and control groups (Figure 1) [48].

Descriptive statistics will be presented as mean ± standard deviation, or median with range, as appropriate. Parametric analyses will be used for all continuous variables. Chi-square analyses will determine associations between categorical variables. For example, the incidence, severity and type of nausea and vomiting between the two groups. Pearson correlation analysis of continuous variables will be performed. Repeated measures analyses will be conducted to detect between group differences over time as per our statistician recommendations. Statistical significance will be set at p < 0.05 level (two-tailed). Data will be analysed using SPSS for Windows version 22 (Statistical Package for Social Sciences, IL, USA).

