### Predisposing factors influence individual susceptibility to chemotherapy-induced nausea and vomiting

Multiple factors are reported to influence the individual risk of a patient developing CINV [31]. These factors relate not only to the treatment protocol but also the patient’s lifestyle, mental state, and previous experience with nausea and vomiting in other settings [32-34]. Consequently, while the emetogenicity of the treatment protocol is the major determinant of CINV risk, a patient with multiple predisposing factors can experience significant levels of CINV despite being prescribed a low emetogenic chemotherapy regimen. Of particular concern is the development of anticipatory nausea and vomiting, a conditioned response that is difficult to treat, and the gradual resistance to anti-emetic therapy after multiple chemotherapy cycles [35].

These factors represent a significant set of potential confounding variables for RCTs in this setting. To date, all trials in this area have recruited patients that have already experienced nausea and vomiting in previous chemotherapy cycles. This allows for the potential recruitment of patients with an already established resistance to additional anti-emetic therapies. Furthermore, if lifestyle factors such as alcohol intake and previous experience of motion sickness, which have been shown to influence CINV risk, are not screened for, this may result in a study comprised of two groups with a predisposed heterogeneous response to CINV. To date, this has not been thoroughly controlled for and therefore, may account for some of the difference in the results between previous trials. We have developed a short questionnaire that aims to assess these factors and will be the first study to factor this into our post-study statistical analysis.

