### Outcomes

#### Primary outcomes

• The frequency, severity, duration of acute and delayed nausea

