### Questionnaires used

#### Rhodes Inventory of Nausea, Vomiting and Retching (INVR)

The INVR is a self-report questionnaire that measures nausea, vomiting and retching as separate entities based on 8 items with 5-point Likert scales [30]. The frequency and distress of all entities is measured as well as the duration of nausea and the amount of vomitus. The tool is suitable for use during each phase of CINV (i.e anticipatory, acute, and delayed) and is designed to measure symptoms over a 12 hour period; however, for the purpose of this trial, this period was extended to 24 hours to reduce the study burden on patients. It takes less than 5 minutes to complete.

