### Functional Assessment of Cancer Therapy- General (FACT-G) and Fatigue (FACIT-F) subscale

The participants’ self-assessed QoL will be measured using the FACT-G questionnaire, a validated tool that has been widely used in this setting [47]. It contains 27 questions with a 5-point scale, which assesses four domains of patient QoL: physical well-being, social/family well-being, emotional wellbeing, and functional well-being. Strong concurrent validity with the Functional Living Index-Cancer tool was demonstrated with a Pearson coefficient of 0.79 [47]. Additionally, we have included the Functional Assessment of Chronic Illness Therapy- Fatigue (FACIT-F) subscale, a 13 item Likert scale, to assess self-reported symptoms of fatigue before and after each chemotherapy cycle. It is estimated to take between 5-10 minutes to complete.

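### Chi-square is named for graded nausea severity, which discards the order of the grades and leaves out the emetogenicity strata used to randomise

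*Protocol article*

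**What the plan says.** On allocation, the Statistical analysis section of the protocol article states: "Participants will be block stratified by chemotherapy category". It lists four levels, from minimal to high, and allocates to the two arms inside each level. The Background section on predisposing factors explains why that factor matters: "the emetogenicity of the treatment protocol is the major determinant of CINV risk".

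On analysis, the Statistical analysis section states: "Chi-square analyses will determine associations between categorical variables". Its illustration follows at once: "For example, the incidence, severity and type of nausea and vomiting between the two groups". The same section also names parametric analyses for continuous variables, Pearson correlation, and repeated measures analyses for group differences over time. The form of the repeated measures analyses is left to the statistician's advice. None of the named methods is said to use the strata.

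The primary outcome is given as "The frequency, severity, duration of acute and delayed nausea". The Rhodes INVR, the instrument for nausea, "measures nausea, vomiting and retching as separate entities based on 8 items with 5-point Likert scales".

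**The concern.** Two separate features of the named chi-square deserve attention.

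- **Order.** A Pearson chi-square on a two-by-k table treats the k grades as unrelated labels. A treatment that shifts patients towards milder grades is then tested on k − 1 degrees of freedom instead of one. The test stays valid but spends power on patterns nobody expects.
- **Strata.** Stratified randomisation balances the arms on emetogenicity, so the true variance of the treatment comparison excludes the between-stratum part. A test that ignores the strata still counts that part. If the strata are prognostic, the test rejects too rarely under the null and forgoes power under the alternative.

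At stake is efficiency on a component of the primary outcome. Neither feature makes a positive result invalid.

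**Working it through.** **Inputs from the protocol article.** 73 per arm, 146 in total, 80% power, two-sided 5% (Sample size); four strata (Statistical analysis); 5-point items (INVR section). The article gives no effect size, standard deviation, category split, block size or strength of the strata, so these are assumed below.

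**The plan's own figure.** The 73 per arm cannot be reproduced from stated inputs, because none are printed. Back-solving for two means gives d = (1.960 + 0.842) × √(2/73) = 0.464 (0.467 with the t distribution). Several pairs of proportions, such as 60% against 37% or 40% against 19%, also give 73. I use d = 0.464 only as a reference point.

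**1. Cost of ignoring order, worked example.** Assume a control split of 40/25/15/12/8% from mildest to worst grade and a common odds ratio of 2.3.

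- Control cumulative proportions: 0.40, 0.65, 0.80, 0.92. Multiplying each cumulative odds by 2.3 gives 0.605, 0.810, 0.902, 0.964 in the ginger arm, i.e. a split of about 60.5/20.5/9.2/6.2/3.6%.
- Chi-square non-centrality = 73 × Σ[(p_c − p̄)²/p̄ + (p_g − p̄)²/p̄] = 6.97. With 4 df the 5% critical value is 9.488, so power = 0.54.
- Simulation agrees: chi-square 0.53, Mann-Whitney 0.75. At an odds ratio of 2.5 the pair is 0.62 against 0.83.

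**2. Dependence on the number of grades.** Take a shift that has 80% power on 1 df, so non-centrality = (1.960 + 0.842)² = 7.85, and spread it over k − 1 df:

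| Grades | df | Power of chi-square | Per arm for 80% |
|---|---|---|---|
| 2 | 1 | 0.800 | 73 |
| 3 | 2 | 0.709 | 90 |
| 4 | 3 | 0.645 | 102 |
| 5 | 4 | 0.595 | 112 |

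**3. Does chi-square on ordered grades have the wrong size?** In simulation (146 patients, four strata with assumed shares 10/20/36/34%, blocks of 4, five grades, 4,000 runs) with strata that are not prognostic, its size was 0.049. Power was 0.543 against 0.746 for a trend test, at a log-odds effect of 0.85. Ignoring order therefore costs power only.

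**4. Cost of ignoring prognostic strata, continuous endpoint.** Let R² be the share of outcome variance explained by the strata.

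- Size of the unadjusted test = 2Φ(−1.960/√(1 − R²))
- Power unadjusted = Φ(0.842/√(1 − R²))
- Power adjusted = Φ(2.802/√(1 − R²) − 1.960)

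| R² (assumed) | Size, unadjusted | Power, unadjusted | Power, adjusted |
|---|---|---|---|
| 0.05 | 0.044 | 0.806 | 0.820 |
| 0.10 | 0.039 | 0.813 | 0.840 |
| 0.20 | 0.028 | 0.827 | 0.879 |

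**5. Both features together.** In the simulation of step 3, with the log-odds of worse nausea rising by 0.5 to 1.5 per stratum, the unstratified 5-level chi-square had size 0.044 to 0.037 and power 0.51 to 0.30. A stratified mean-score test had size 0.052 to 0.058 and power 0.73 to 0.69. The upper end of that range is a very strong stratum effect. The Monte Carlo standard error of a size near 0.05 is √(0.05 × 0.95/4,000) = 0.003.

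**The case against.** The best defence is that chi-square appears as an example for categorical variables and is not declared the primary test. The article also names parametric and repeated measures analyses, and sizes the trial on unpaired t-tests. The INVR section lists frequency, distress, duration and amount, with no item called severity, so it is not certain that severity will be a 5-level variable. With three grades the loss is about 9 percentage points (0.80 to 0.709). All this limits the size of the point. It does not remove it: grades of severity are ordered however they are formed, and the text names an unordered test for them.

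Four stronger readings are tempting, and the document supports none of them.

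- **That the whole analysis ignores the strata.** For the repeated measures analyses this is only silence. Their terms are left to the statistician, and a condensed article may leave them to a fuller plan. The Background also promises to bring susceptibility factors into the analysis, so some adjustment is intended, although it does not name the stratum.
- **That chi-square on ordered grades is itself conservative.** Step 3 shows that it holds its size. Conservatism comes only from omitting prognostic strata.
- **That the trial falls below its planned power.** For a continuous endpoint, step 4 shows unadjusted power above 80% at every R² considered. A gain is forgone.
- **That pre-chemotherapy values in cycles 2 and 3 will serve as baselines and hide a carried-over benefit.** The FACIT-F text says the subscale is there "to assess self-reported symptoms of fatigue before and after each chemotherapy cycle". That is a schedule of assessments. No baseline or change score is defined from it.

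**Conclusion.** The point holds in a limited form. The article names an unordered, unstratified test for the severity of nausea, which is part of the primary outcome. If severity is kept in five ordered grades, power at 73 per arm is about 54% where a rank test would have about 75%, given the assumed split and odds ratio; fewer grades narrow the gap. Separately, if emetogenicity is prognostic, an unstratified test has a true two-sided size of about 0.044 to 0.028 for an assumed R² of 0.05 to 0.20 and gives up roughly 1 to 5 percentage points of power on a continuous endpoint (0.820 − 0.806 to 0.879 − 0.827).

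The direction of both effects is certain under those conditions. Their size rests on assumptions, because the article gives no category split, effect size or stratum effect. The error runs towards missing a real benefit and does not produce false positives.

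**What to change.** - For graded severity of nausea and vomiting, replace chi-square with a proportional-odds model that includes the emetogenicity stratum, or with a stratified (van Elteren) Wilcoxon test.
- For incidence, use a Cochran-Mantel-Haenszel test stratified by emetogenicity.
- State that the repeated measures analyses include the stratum as a fixed effect.
- Say in advance that the minimal and low strata will be merged if either is sparse.
- State how severity is derived from the INVR and in how many grades.

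The cost is analysis wording. The stratum must be known for every participant in order to randomise, so no data are added. The proportional-odds model brings its own assumption of a common odds ratio across grades; the van Elteren test avoids fitting that model.

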**Methods/Design:**

In a double–blinded randomised-controlled trial, chemotherapy-naïve patients will be randomly allocated to receive either 1.2 g of a standardised ginger extract or placebo per day. The study medication will be administrated as an adjuvant treatment to standard anti-emetic therapy and will be divided into four capsules per day, to be consumed approximately every 4 hours (300 mg per capsule administered q.i.d) for five days during the first three cycles of chemotherapy. Acute, delayed, and anticipatory symptoms of nausea and vomiting will be assessed over this time frame using a valid and reliable questionnaire, with nausea symptoms being the primary outcome. Quality of life, nutritional status, adverse effects, patient adherence, cancer-related fatigue, and CINV-specific prognostic factors will also be assessed.

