### Hypothesis

It is hypothesised that in chemotherapy-naïve medical oncology patients about to commence treatment of any emetogenicity, adjuvant ginger supplementation compared with placebo will:

1. Reduce the frequency, distress and duration of chemotherapy-induced nausea (i.e. acute, delayed and anticipatory) during each chemotherapy cycle (up to 3 cycles).

2. Reduce frequency, distress and duration of chemotherapy-induced vomiting and retching

3. Result in improved nutritional status, physical function and quality of life

4. Be adhered to (>80% consumption of supplements) and well tolerated (no significant adverse events related to ginger supplementation).

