### Investigational plan

#### Overall study design

This study will be a double-blinded, randomised, placebo-controlled trial. Outcomes will be assessed at three days prior to chemotherapy, one day prior to chemotherapy, on the day of chemotherapy, and during the 4 days post-chemotherapy. Participants will consume the study medication for 5 days per chemotherapy cycle, commencing on the day of chemotherapy. This will be repeated over 3 chemotherapy cycles.

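### Six unranked primary nausea outcomes share one unadjusted 5% threshold, while the sample size is for a single comparison on a measure that is not among the six

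*Protocol article*

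**What the plan says.** All references are to the protocol article.

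- **Primary outcomes** has a single entry: "The frequency, severity, duration of acute and delayed nausea". Three domains in two phases make six outcomes, and none is put first.
- **The abstract** (Methods/Design) is no more specific: "with nausea symptoms being the primary outcome".
- **Hypothesis**, item 1, uses a different set: "Reduce the frequency, distress and duration of chemotherapy-induced nausea (i.e. acute, delayed and anticipatory) during each chemotherapy cycle (up to 3 cycles"). Distress stands where the outcome list has severity, and anticipatory nausea is added.
- **Statistical analysis** states the threshold once, for everything: "Statistical significance will be set at p < 0.05 level (two-tailed"). On time it says "Repeated measures analyses will be conducted to detect between group differences over time as per our statistician recommendations". It does not say whether that yields one test per outcome or one per cycle.
- **Sample size** gives 73 per group (N = 146) for one unpaired comparison of two means, at 80% power and two-sided 5%. The effect is taken from a reduction in the prevalence of nausea in a cited study.
- **The description of the INVR** lists frequency and distress for each symptom, plus duration of nausea and amount of vomitus. It describes no nausea severity item.

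**The concern.** An error rate of 5% and a power of 80% belong to a specific test. Here the outcome list offers six candidates, the hypothesis offers a partly different set, and the sample size rests on a seventh quantity, prevalence. No passage says which result decides the trial, or whether one significant outcome is enough or all are needed.

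The Background calls the existing evidence contentious, and the Discussion says that a successful trial would support ginger as an adjuvant anti-emetic. If success is undefined, a report could lead with whichever nausea outcome crossed 5%, and a reader could not tell how surprising that result was.

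**Working it through.** **1. The plan's own figure.** The document gives no mean difference, standard deviation or prevalence rates, so 73 per group cannot be reproduced forwards. Solving backwards for one two-sided 5% test at 80% power:

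d = (z₀.₉₇₅ + z₀.₈₀) × √(2/n) = (1.960 + 0.842) × √(2/73) = 0.464

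The noncentral t gives 0.467. So 73 per group fits one test at a standardised difference of about 0.46 to 0.47. This is a back-solved value, not one stated in the plan.

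**2. Number of primary tests.** 3 domains × 2 phases = 6, taking the repeated-measures analysis to give one test per outcome with cycles pooled. This is the smallest count that the outcome list supports without a composite.

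**3. If any one of six counts as success.** Under independence the chance of at least one false positive is 1 − 0.95⁶ = 0.265.

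The outcomes come from the same patients and the same kind of self-report, so they will be positively correlated. The document gives no correlations; those below are assumptions. For equicorrelated normal test statistics, each tested at |Z| > 1.96:

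| Assumed correlation | Chance of at least one false positive, 6 tests |
|---|---|
| 0 (ceiling) | 26.5% |
| 0.5 | 20.7% |
| 0.7 | 16.4% |
| 0.9 | 10.8% |
| 0.95 | 8.9% |

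Every row exceeds 5%. Over the range 0.5 to 0.9 the inflation is about two to four times.

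**4. If all six must succeed.** The false-positive rate is then at most 5%, but the power changes. Assume, generously, that each outcome alone has 80% power. Under independence the joint power is 0.8⁶ = 0.262. On the same correlated model it is 48%, 57% and 68% at correlations 0.5, 0.7 and 0.9. None reaches 80%.

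**5. If an adjustment were added later and all six kept.** Take Bonferroni as an illustration; the plan does not propose it. The per-test level is 0.05/6 = 0.00833, with critical value 2.638. At the back-solved d of 0.464, power per outcome at 73 per group is Φ(2.802 − 2.638) = 56%. Restoring 80% needs 2 × (2.638 + 0.842)² / 0.464² ≈ 113 per group (N = 226).

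**6. Matching the sample size to an outcome.** The basis is prevalence. The six outcomes are frequency, severity and duration, each acute and delayed. None of them is prevalence, so the Sample size section does not show which of the six was meant to lead.

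**The case against.** **The threshold is general.** The plan does not say that each outcome gets its own decisive test, or that one significant result is success. Hypothesis 1 joins its domains with "and"-type wording, and the abstract speaks of one primary outcome. This stands: the any-one reading is something the text fails to exclude, not a rule it states. But the other reading, that all must succeed, leaves the 80% power without support, so neither reading rescues the plan.

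**Eighteen tests.** A reader might multiply six outcomes by three cycles, because the hypothesis speaks of an effect "during each chemotherapy cycle (up to 3 cycles"), and quote 1 − 0.95¹⁸ = 60%. The documents do not support that as the plan. The six come from the outcome list and the cycles from a hypothesis with a different set, which would itself give 3 × 3 = 9 combinations, or 27 by cycle. The planned repeated-measures analysis may well pool the cycles. Separate tests per cycle are one possible reading and would raise the error further, but the point does not need them.

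**Two analyses of the same data.** A reader might infer that chi-square and repeated-measures tests compete for all the primary outcomes. The article says "Chi-square analyses will determine associations between categorical variables" and gives incidence, severity and type as examples. Only severity clearly overlaps the primary list.

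**A condensed article, with no analysis plan shown.** A multiplicity procedure and the exact model are often left to that plan, and their absence alone would be no finding. What the article does fix is several co-equal primary outcomes and a sample size for one comparison. An analysis plan that picked one outcome would be changing the article's list; one that adjusted for six would undercut its power.

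**Conclusion.** The concern holds on the six listed outcomes alone. As written, the trial has no identifiable primary test. Depending on how success is read, either the chance of a false primary claim is above 5% or the power of the primary claim is below the stated 80%.

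The size in the first case is about 11% to 21% for six tests with cycles pooled, at assumed correlations of 0.9 to 0.5. The figure of 26.5% is the independence ceiling and should not be read as the expected value. In the second case the error is controlled, and the joint power depends on the correlations and on the assumption of 80% per outcome.

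The correlations and the standardised difference are not in the document. The direction of the conclusion does not depend on their exact values: the any-one error is still 8.9% at a correlation of 0.95. Naming the primary endpoint belongs in the protocol and needs settling before unblinding.

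**What to change.** Before unblinding:

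1. Name one primary nausea measure, phase and time point, or one repeated-measures contrast across cycles. Test it once at two-sided 5% with one named model.
2. Make the other domains, the other phase and any cycle-specific results secondary, tested in a fixed order or by Holm.
3. Rewrite the sample-size statement for that endpoint, with the assumed difference and standard deviation (or rates) shown.
4. Reconcile severity in the outcome list with distress in the hypothesis and in the INVR description, so that the named endpoint is one the instrument measures.

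One example is the sum of the INVR nausea items over the delayed-phase days of cycle 1. It is not the required choice. It would use distress rather than severity and would make cycles 2 and 3 secondary, so the sponsor would have to accept both openly.

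The cost is wording in the protocol and the registry entry. With a single test, multiplicity adds nothing to N = 146, although restating the sample size for the chosen endpoint may change that number for other reasons. The sponsor gives up the freedom to claim primary success on whichever outcome turns out best.
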